**6.2.5. Criteria for dose reduction (Arm A)**

When resuming administration in patients with adverse events that meet the dose reduction criteria specified in Table 4, the dose should be reduced one step at a time according to “Dose reduction levels” in Table 5. However, the minimum dose of S-1 is 50 mg/day, and the dose will not be increased again after a dose reduction. For adverse events other than those listed in Table 4, the S-1 dose may be reduced at the discretion of the treating physician, again in accordance with the dose reduction levels listed in Table 5.

**Table 4. Criteria for dose reduction**

| Item                                     | Criteria for dose reduction                                                            |
|------------------------------------------|----------------------------------------------------------------------------------------|
| White blood cell count                   | $< 1,000/\text{mm}^3$ (Grade 4)                                                        |
| Neutrophil count                         | $< 500/\text{mm}^3$ (Grade 4)
Febrile neutropenia (Grade 3 or higher)               |
| Platelet count                           | $< 25,000/\text{mm}^3$ (Grade 4)
Grade 3 thrombocytopenia with platelet transfusion |
| Creatinine                               | $\geq 1.2\text{ mg/dL}$                                                                |
| Total bilirubin                          | $\geq 2.0\text{ mg/dL}$                                                                |
| Non-hematologic toxicity (except low Na) | Grade 3 and above                                                                      |

Grade 4 non-hematologic toxicities (Grade 1 or higher for pulmonary inflammation) will result in discontinuation of protocol treatment.

**Table 5. Dose reduction levels (dose reduction methods for S-1)**

| Body surface area                             | At the start of treatment
(FT equivalent) | Dose reduction level |                        |                        |                        |
|-----------------------------------------------|----------------------------------------------|----------------------|------------------------|------------------------|------------------------|
|                                               |                                              | -1                   | -2                     | -3                     | -4                     |
| $< 1.25\text{ m}^2$                           | 80 mg/day                                    | 50 mg/day            | Cessation of treatment | -                      | -                      |
| $\geq 1.25\text{ m}^2$ and $< 1.5\text{ m}^2$ | 100 mg/day                                   | 80 mg/day            | 50 mg/day              | Cessation of treatment | -                      |
| $\geq 1.5\text{ m}^2$                         | 120 mg/day                                   | 100 mg/day           | 80mg/day               | 50 mg/day              | Cessation of treatment |

**6.2.6. Criteria for dose escalation (Arm A)**

After 43 days of treatment, if no adverse events are observed that would result in withdrawal/dose reduction and

the physician in charge determines that there are no safety issues, the dose of S-1 may be increased by one step only from the initial standard dose in accordance with “Dose escalation levels” in Table 6.

The dose should not be increased in patients whose dose has been reduced since the first dose due to the CCr value at the time of registration ( $40 \leq \text{CCr} < 60$ ).

The dose should not be increased again in cases where the dose has been reduced.

Dose reductions for increased doses follow the dose reduction levels in Table 7.

**Table 6. Dose escalation levels**

| The method for the dose escalation of S-1       |                                          |                       |
|-------------------------------------------------|------------------------------------------|-----------------------|
| Body surface area                               | Initial standard dose
(FT equivalent) | Dose escalation level |
|                                                 |                                          | +1                    |
| $< 1.25 \text{ m}^2$                            | 80 mg/day                                | 100 mg/day            |
| $\geq 1.25 \text{ m}^2$ and $< 1.5 \text{ m}^2$ | 100 mg/day                               | 120 mg/day            |
| $\geq 1.5 \text{ m}^2$                          | 120 mg/day                               | 150 mg/day            |

**Table 7. Dose reduction levels for the cases with dose escalation**

| The method for the dose reduction for the cases with dose escalation of S-1 |                                        |                      |            |                        |
|-----------------------------------------------------------------------------|----------------------------------------|----------------------|------------|------------------------|
| Body surface area                                                           | Dose after increase
(FT equivalent) | Dose reduction level |            |                        |
|                                                                             |                                        | -1                   | -2         | -3                     |
| $< 1.25 \text{ m}^2$                                                        | 100 mg/day                             | 80 mg/day            | 50 mg /day | Cessation of treatment |
| $\geq 1.25 \text{ m}^2$ and $< 1.5 \text{ m}^2$                             | 120 mg/day                             | 100 mg/day           | 80 mg/day  | 50 mg/day              |
| $\geq 1.5 \text{ m}^2$                                                      | 150 mg/day                             | 120 mg/day           | 100 mg/day | 80 mg/day              |

### 6.2.7. Criteria for completion of protocol treatment (Arm A)

Protocol treatment is terminated when one year has elapsed from the date of the first administration of S-1 as adjuvant chemotherapy after surgery for lung cancer.

### 6.2.8. Administration Simulation (Arm A)

[figure not shown]

### 6.3. Arm B: S-1 2-week administration followed by 1-week rest method

#### 6.3.1. Treatment schedule for Arm B (S-1 2-week administration followed by 1-week rest method)

**Administration cycle:** Oral administration every day for 14 consecutive days from Day 1 (after dinner on Day 1 to after breakfast on Day 15)

The drug is then withdrawn for 7 days, and this is repeated every 3 weeks for one course.

**End date of treatment:** Administration should be performed until the total treatment period from the protocol treatment start date has reached 12 months. No new courses should be started after the same calendar day 12 months after the protocol treatment start date. The final course of treatment should be administered until a date equivalent to day 14.

[figure not shown]

#### Starting dose and starting method

The daily dose of S-1 is calculated according to body surface area from Table 8. “S-1 initial standard dose and one-step dose reduction” and divided equally into two portions and administered orally after breakfast and dinner. If the creatinine clearance (CCr) at the time of enrollment is between 40 mL/min and 60 mL/min, S-1 should be started at a dose reduced by one step from the initial standard dose according to Table 8. If the patient’s body weight has decreased by more than 10% from the baseline, the dose is recalculated and the baseline body weight is considered to be the weight at the time of recalculation.

**Table 8. S-1 initial standard dose and one-step dose reduction**

| Body surface area                              | Initial standard dose (FT equivalent)
(CCr ≥ 60) | Dose reduction level -1
(40 ≤ CCr < 60) |
|------------------------------------------------|-----------------------------------------------------|--------------------------------------------|
| < 1.25m                            | 80 mg/day                                           | 50 mg/day                                  |
| ≥ 1.25 m  and < 1.5 m  | 100 mg/day                                          | 80 mg/day                                  |
| ≥ 1.5m                             | 120 mg/day                                          | 100 mg/day                                 |

#### 6.3.2. Course start criteria for Arm B (S-1 2-week administration followed by 1-week rest)

The start of the next course is decided after confirming that all of the criteria in Table 9 below are met on the day before or the day of the scheduled start of the course. If even one of the criteria is not met, administration is postponed, and administration is started as soon as the patient recovers.

However, for the start of the second and subsequent courses, **if these criteria are not met 21 days beyond the scheduled start of the next course, the study of the case will be terminated** (see figure below).

In the case of a postponement of the start of a course, the start date after the postponement shall be Day 1 of the course.

If recurrence is observed during the course of treatment, protocol treatment should be discontinued at that time.

**Table 9: Course Start Criteria (Arm B)**

| Item              |                        | Criteria for starting the course |
|-------------------|------------------------|----------------------------------|
| Blood toxicity    | White blood cell count | ≥ 3,000/mm           |
|                   | Neutrophil count       | ≥ 1,500/mm           |
|                   | Platelet count         | ≥ 100,000/mm         |
| Non-hematological | Total bilirubin        | ≤ 1.5 mg/dL                      |

|          |                                                |                                                                                         |
|----------|------------------------------------------------|-----------------------------------------------------------------------------------------|
| toxicity | AST and ALT                                    | $\leq 100$ IU/L                                                                         |
|          | Creatinine                                     | $< 1.2$ mg/dL                                                                           |
|          | Pneumonia                                      | Grade 0                                                                                 |
|          | Infection                                      | No fever with infection                                                                 |
|          | PS                                             | 0 to 1                                                                                  |
|          | Other subjective and general clinical findings | Grade 2 or below (but may be administered at the discretion of the physician in charge) |

[figure not shown]

### 6.3.3. Criteria for in-course withdrawal and resumption (Arm B)

If an adverse event that meets the criteria in Table 10 develops during S-1 administration, S-1 will be withdrawn. If the adverse event has not resolved by the end of breakfast on Day 15, no further S-1 should be administered for that course. If the patient has not recovered from a Grade 4 non-hematologic toxicity (Grade 1 or higher for pulmonary inflammation), protocol treatment should be discontinued.

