**6.2.4. Criteria for resumption of administration (Arm A)**

When restarting the drug after suspension, make sure that the “Criteria for resumption of administration” in Table 3 are met. However, if the adverse event meets the “Dose Reduction Criteria” in Table 4, the dose should be reduced from the time of resumption. If the drug is suspended due to an adverse event other than those listed in Table 2 “Criteria for continuing administration”, the grade of the adverse event that caused the suspension must have improved by at least one level, and the physician in charge must determine that the drug can be administered.

If S-1 treatment cannot be resumed after 28 days, protocol treatment should be discontinued.

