|                            | Creatinine                     | $\geq 1.2$ mg/dL                                                                                                                                                 | $< 1.2$ mg/dL                                                                                                    |
|                            | Infection                      | Fever of suspected infection                                                                                                                                     | No fever of suspected infection                                                                                  |
|                            | PS                             | 2 or more                                                                                                                                                        | 0 to 1                                                                                                           |
|                            | Diarrhea, mouth ulcers         | Grade 2 or above                                                                                                                                                 | Grade 1 or below                                                                                                 |
|                            | Other non-hematologic toxicity | Grade 3 or above                                                                                                                                                 | Grade 2 or below
(However, the physician in charge may decide in his/her discretion to allow administration.) |
|                            | Others                         | Drug withdrawal is allowed when deemed necessary by the physician in charge due to the occurrence of adverse events that do not fall under the above categories. | Adverse event that caused withdrawal from the drug is in remission                                               |

Grade 4 non-hematologic toxicities (Grade 1 or higher for pulmonary inflammation) will result in discontinuation of protocol treatment.

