#### 6.3.4. Criteria for dose reduction (Arm B)

When resuming dosing in patients with adverse events that meet the criteria for dose reduction specified in Table 11, the dose should be reduced one step at a time according to Table 12, “Dose reduction levels”. However, the minimum dose of S-1 is 50 mg/day, and the dose will not be increased again after a dose reduction. For adverse events other than those listed in Table 11, the S-1 dose may be reduced at the discretion of the physician in charge, again in accordance with the dose reduction levels listed in Table 12.

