## **7. Protocol treatment discontinuation, termination criteria, and subsequent therapy**

### **7.1. Criteria for discontinuation of protocol treatment**

If any of the following criteria are met, the physician in charge will discontinue protocol treatment

- 1) If protocol treatment cannot be started 28 days after the last day of S-1 treatment (which corresponds to 21 days after the scheduled start of the next course in Arm B) (in this case, the day after the last day of S-1 treatment is considered Day 1). Starting administration on the same day of the week is acceptable).
- 2) If a withdrawal of more than 28 days is required (in this case, the day after the last day of S-1 administration shall be considered as Day 1. Resumption on the same day of the week 4 weeks after the date of the last dose is acceptable)
- 3) When an adverse event that meets each of the dose reduction criteria occurs even if the S-1 dose is reduced to the lowest level  
Or if a Grade 4 non-hematologic toxicity (Grade 1 or higher for pulmonary inflammation) develops.
- 4) When an adverse event occurs that makes it difficult to continue administration
- 5) If the physician in charge determines that the disease has recurred
- 6) If the patient requests discontinuation
- 7) When matters that should be excluded from the subjects turned out after registration
- 8) Other cases in which the physician in charge deems it necessary to discontinue the study.

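### Arm B, Section 6.3.3 makes the stop for Grade 4 non-hematologic toxicity or any pulmonary inflammation depend on non-recovery, whereas 7.1(3) and the Table 10 and 11 footnotes stop treatment once the event develops

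*Protocol*

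**What the plan says.** Four statements in the protocol govern what happens in Arm B after a Grade 4 non-hematologic toxicity, or after pulmonary inflammation of Grade 1 or more.

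- **Section 6.3.3**, last sentence of the text before Table 10: "If the patient has not recovered from a Grade 4 non-hematologic toxicity (Grade 1 or higher for pulmonary inflammation), protocol treatment should be discontinued".
- **Footnote to Table 10**, the table that 6.3.3 applies: "Grade 4 non-hematologic toxicities (Grade 1 or higher for pulmonary inflammation) will result in discontinuation of protocol treatment".
- **Footnote to Table 11**, under the Arm B dose-reduction criteria: the same sentence as under Table 10.
- **Section 7.1, criterion 3)**, which covers both arms: "Or if a Grade 4 non-hematologic toxicity (Grade 1 or higher for pulmonary inflammation) develops". The lead-in to 7.1 has the physician discontinue protocol treatment if any listed criterion is met.

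Arm A carries the unconditional footnote under Table 4. Its text has no sentence that makes this stop depend on recovery.

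**The concern.** The same events, described in the same terms, trigger a conditional stop in one place and an unconditional stop in three others. The conditional version stands in the operational section, which a site would consult when toxicity appears during a course. That section covers resumption as well as withdrawal, so its reader is looking for whether and when S-1 may restart.

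At stake is a safety rule. Eligible patients are 75 or older and have had a lobectomy or a larger resection. A physician who takes 6.3.3 at its word could wait for a Grade 4 event or lung inflammation to settle and then give S-1 again, although 7.1(3) requires protocol treatment to end. The sentence also sets no time at which recovery is to be judged. The sentence before it mentions breakfast on Day 15, but only to decide whether more S-1 is given in that course.

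**Working it through.** No arithmetic applies. The check sets the four statements side by side for a patient in whom the event has occurred.

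| State of the patient | 6.3.3, last sentence | Table 10 footnote | Table 11 footnote | 7.1(3) |
|---|---|---|---|---|
| Not recovered | stop | stop | stop | stop |
| Recovered | no stop ordered; resumption implied | stop | stop | stop |

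1. **Unrecovered patient.** All four statements agree.

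2. **Recovered patient.** The footnotes and 7.1(3) refer only to the event having occurred, and later recovery does not undo that. Section 6.3.3 orders a stop only for the unrecovered patient. It does not say outright that a recovered patient may resume. But if recovered and unrecovered patients were both to stop, the condition would have no function. The natural reading is therefore that recovery changes the outcome.

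3. **Which rule is meant.** Under 7.1 one met criterion is enough, and 7.1(3) is met when the event develops. The two Arm B footnotes agree with it, as does the Arm A footnote under Table 4. Nothing in the protocol limits 7.1(3) or the footnotes to events that fail to resolve. The count for Arm B is one conditional statement against three unconditional ones, and the general discontinuation section is among the three. The unconditional rule is the intended one. The wording of 6.3.3 may be a slip of drafting or translation.

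4. **Size.** An expected number of affected patients would need the frequency of these events in Arm B and the share that recover. The protocol gives neither, so no number follows.

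**The case against.** **There is no strict contradiction.** Section 6.3.3 says what to do if the patient has not recovered and is silent otherwise. A site that stops whenever the event develops breaks none of the four statements. As logic this stands. It does not rescue the sentence, because an instruction whose condition is meant to have no effect will mislead the person who has to act on it.

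**The protocol settles the matter elsewhere.** Section 7.1 is decisive once any criterion is met, and the unconditional footnote stands in the same subsection as the faulty sentence. A site would have to overlook that footnote, its repeat under Table 11 and 7.1(3) to go wrong. This also stands, and it is why the point is minor.

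**Stronger readings that a reader might infer.** The documents do not support them.

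- *That the tables themselves permit restart.* Section 6.3.2 says that when a course-start criterion fails, "administration is postponed, and administration is started as soon as the patient recovers", and Table 9 lists pneumonia at Grade 0. A Grade 0 entry condition is compatible with a separate permanent stop, and the protocol does not say that pneumonia in the tables and pulmonary inflammation in the stop rule are the same event. Table 10 has the row "Other non-hematologic toxicity | Grade 3 or above", and 6.3.4 says "When resuming dosing in patients with adverse events that meet the criteria for dose reduction specified in Table 11, the dose should be reduced", where Table 11 includes Grade 3 and above. These are general rules to which the footnotes make an exception for Grade 4. Arm A is built the same way: see 6.2.5, "When resuming administration in patients with adverse events that meet the dose reduction criteria specified in Table 4, the dose should be reduced", and 6.2.4, "the dose should be reduced from the time of resumption", both subject to the Table 4 footnote.
- *That Table 10, having no pneumonia row, leaves Grade 1 or 2 lung inflammation to the faulty sentence and the footnote alone.* Its last row also lets the physician withdraw the drug for events outside the listed categories and resume on remission. That row does not settle the conflict, but it means the list of applicable instructions is longer.
- *That the sentence biases the comparison of arms or inflates Arm B completion.* Section 7.3 requires that no 7.1 criterion was met, and 12.2 requires that the reduction and withdrawal rules were followed. A patient restarted against 7.1(3) meets neither condition. With no event frequency given, a shift in the completion rate cannot be shown in either direction.

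**Conclusion.** The last sentence of 6.3.3 is wrong as written. It turns an unconditional stop rule into one that depends on non-recovery, against 7.1(3) and the footnotes to Tables 10 and 11. The severity is minor: the intended rule can be recovered from the protocol, and harm would require a site to follow the one faulty statement and miss three correct ones. The possible harm is giving S-1 again to an elderly patient who should have stopped. The number of such patients cannot be computed.

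The conclusion rests on one step of interpretation, that a condition of non-recovery implies different handling after recovery. It does not depend on equating pneumonia with pulmonary inflammation, because the conflicting statements all use the same terms.

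**What to change.** Replace the last sentence of the 6.3.3 text with an unconditional one that points to 7.1(3). For example: *Protocol treatment ends as soon as an event named in the second part of 7.1(3) develops, whether or not the patient later recovers.* Repeating the 7.1(3) wording itself would serve equally well.

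Leave the tables alone. Limiting the Table 10 row for other non-hematologic toxicity to Grade 3 would take Grade 4 out of the withdrawal trigger. A note against restart at the pneumonia rows of Tables 3 and 9 could bar patients who have recovered from ordinary pneumonia, which would be a new clinical rule.

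The cost is one sentence and the change application that Section 16.7 requires. There are no added visits, procedures or patients, and the sample size and analysis do not change.
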